# A randomized double-blind clinical trial on safety and efficacy of tauroursodeoxycholic acid (TUDCA) as add-on treatment in patients affected by amyotrophic lateral sclerosis (ALS): the statistical analysis plan of TUDCA-ALS trial

**DOI:** 10.1186/s13063-023-07638-w

**Published:** 2023-12-05

**Keywords:** Statistical analysis plan, Randomized, Double-blind, Clinical trial, Phase III, Amyotrophic lateral sclerosis, Bile acids

## Abstract

**Background:**

Amyotrophic lateral sclerosis (ALS) is a highly debilitating neurodegenerative condition. Despite recent advancements in understanding the molecular mechanisms underlying ALS, there have been no significant improvements in therapeutic options for ALS patients in recent years. Currently, there is no cure for ALS, and the only approved treatment in Europe is riluzole, which has been shown to slow the disease progression and prolong survival by approximately 3 months. Recently, tauroursodeoxycholic acid (TUDCA) has emerged as a promising and effective treatment for neurodegenerative diseases due to its neuroprotective activities.

**Methods:**

The ongoing TUDCA-ALS study is a double-blinded, parallel arms, placebo-controlled, randomized multicenter phase III trial with the aim to assess the efficacy and safety of TUDCA as add-on therapy to riluzole in patients with ALS. The primary outcome measure is the treatment response defined as a minimum of 20% improvement in the ALS Functional Rating Scale-Revised (ALSFRS-R) slope during the randomized treatment period (18 months) compared to the lead-in period (3 months). Randomization will be stratified by country. Primary analysis will be conducted based on the intention-to-treat principle through an unadjusted logistic regression model. Patient recruitment commenced on February 22, 2019, and was closed on December 23, 2021. The database will be locked in September 2023.

**Discussion:**

This paper provides a comprehensive description of the statistical analysis plan in order to ensure the reproducibility of the analysis and avoid selective reporting of outcomes and data-driven analysis. Sensitivity analyses have been included in the protocol to assess the impact of intercurrent events related to the coronavirus disease 2019. By focusing on clinically meaningful and robust outcomes, this trial aims to determine whether TUDCA can be effective in slowing the disease progression in patients with ALS.

**Trial registration:**

ClinicalTrials.gov NCT03800524. Registered on January 11, 2019.

**Supplementary Information:**

The online version contains supplementary material available at 10.1186/s13063-023-07638-w.

## Introduction

### Background and rationale

Amyotrophic lateral sclerosis (ALS) is a chronic non-communicable neurodegenerative rare disease that affects approximately 40,000 individuals in Europe, leading to around 11,000 deaths each year [1, 2]. Despite much has been achieved over the last two decades in understanding the disease complexity, there is an urgent need to find disease-modifying therapies that can slow disease progression and extend patient survival. Currently, the only approved treatment in Europe is riluzole, a glutamate release inhibitor, which provides a modest extension of survival in ALS patients. Riluzole has been shown to increase survival by only approximately 3 months [3], but this indicates that modifying disease progression is a realistic goal. Nonetheless, all subsequent drug trials for ALS have failed to deliver improvements in patient care [4].

The ongoing “Safety and efficacy of tauroursodeoxycholic acid as add-on treatment in patients affected by amyotrophic lateral sclerosis” (TUDCA-ALS) study takes advantage of the results of a recent proof-of-concept phase IIb study [5] showing that, in patients who received tauroursodeoxycholic acid (TUDCA) in addition to riluzole, the per-year decline rate of ALS functional rating scale revised (ALSFRS-R) was of about 7 points smaller (on a 0–48 score) compared to riluzole only. The efficacy of TUDCA is further supported by the evidence that TUDCA has cytoprotective properties in animal models of neurodegenerative diseases [6]. Additionally, several clinical studies have shown the safety and tolerability of TUDCA. Therefore, this large-scale, phase III, TUDCA-ALS trial aims to confirm and further evaluate the efficacy of TUDCA as a disease-modifying agent in ALS. The study also incorporates the assessment of reliable biomarkers associated with disease progression and cytoprotective activity during the 18-month treatment period.

### Study objectives

The primary objective of the TUDCA-ALS study is to assess the efficacy of TUDCA, as an add-on therapy to riluzole, in slowing down the progression of ALS throughout the 18-month treatment period, compared to the lead-in phase. The secondary objectives of this study are as follows: (1) to assess the efficacy of TUDCA in slowing disease progression and functional impairment in patients with ALS, as measured by the survival time, the ALSFR-R, the ALS Assessment Questionnaire-40 (ALSAQ-40) and EuroQol 5-Dimension 5L questionnaire (EQ-5D-5L), forced vital capacity (FVC), and the Medical Research Council (MRC) sum-score for muscle force, and (2) to evaluate the long-term safety and tolerability of TUDCA.

The exploratory objective of this study is to investigate the effect of TUDCA on biomarkers associated with disease progression, such as neurofilaments in cerebrospinal (CSF) fluid and serum, serum expression of matrix metalloproteinase-9 (MMP-9) in serum, and plasma creatinine levels.

This document describes in detail the predetermined statistical analysis plan (SAP) for the TUDCA-ALS trial.

## Methods

The analysis outlined in this document is in full compliance with International Conference on Harmonisation ICH E9 guidance [7] and follows the guidelines for the content of statistical analysis plans in clinical trials [8] (Additional file 1).

The SAP (version 2.0 of April 05, 2023) is an update of SAP version 1.3 dated 23 July 2019 and includes the sample size reassessment and additional analyses to account for the COVID-19 pandemic, in alignment with the most recent protocol (version 2.0, 23 July 2021). The SAP has been finalized prior to the completion of the data collection. The study protocol has been registered at www.clinicaltrials.gov (NCT03800524). The updated version of the protocol, providing detailed information on background, design, and rationale, has been published elsewhere [9]. The trial is being conducted in accordance with the Helsinki declaration and the local laws and regulations of the respective countries, prioritizing the highest level of patient protection. The protocol was approved by all the involved ethics committees and by the national regulatory authorities.

### Randomization

Patients are randomized 1:1 to receive TUDCA or placebo. After completing the lead-in period at month 0, eligible patients are randomized by means of a computerized central randomization system and coupled to a unique treatment code through an electronic platform. The randomization list has been generated using STATA software with the “ralloc” command. A permuted block randomization procedure, stratified by country, has been adopted to ensure balance across treatment groups.

### Sample size

The study was powered to assess the potential benefit of TUDCA compared with placebo on the rate of progression, as measured by the ALS-FRS-R total score. The target number of participants was determined based on the expected proportion of responders. In the original planning, based on data from the phase II study [5], a sample size of 199 subjects per arm was calculated to detect a 10% difference between arms assuming a response rate of 10% in the placebo group. This sample size provides at least 80% power with a two-sided alpha of 5%. Considering a dropout rate of 10% at 18 months, a total sample size of 440 patients was planned. Such a sample size provides 83.3% power to detect a 13% absolute difference in survival (defined as death or respiratory insufficiency) between the two treatment groups, corresponding to a hazard ratio of 0.616, assuming an 18-month survival of 60% in the placebo group. However, due to the impact of the COVID-19 outbreak on recruitment [9], the enrolment was planned to be closed at 320 randomized patients. The reassessed sample size allows us to detect an absolute difference of 11% in the proportion of responders between the TUDCA and the placebo arms. It also provides a power of 80% to detect a 14% absolute difference in survival, corresponding to a hazard ratio of 0.58.

### Framework

The aim of the study is to assess the superiority of TUDCA over placebo in terms of efficacy and safety parameters.

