## Statistical principles

Statistical significance will be determined by a two-sided *p*-value ≤ 0.05. Confidence intervals at the 95% level (95% CI) will be reported for all outcomes and measures of association (proportions, means, odds ratios and hazard ratios). Main analyses will be carried out on the intention-to-treat (ITT) population.

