### Safety/harms

All AEs, distinct by severity and relationship with the randomized drug, will be documented and listed. The number and percentage of AEs will be reported, per treatment arm and overall, along with the number and percentage of participants who experienced at least one AE. Moreover, the number of concomitant medications and changes from baseline in vital signs, routine biochemistry and hematology analyses, and in respiratory endpoints will be analyzed. Discrete safety endpoints will be compared using a chi-squared test. The denominator will be the safety population. Continuous safety endpoints will be compared using a *t*-test for parametric variables or the Mann–Whitney test for non-parametric variables. The assumption of normal distribution will be checked using Shapiro–Wilk’s test.

Furthermore, AEs will be described according to the different pandemic periods [18].

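### Safety is framed as superiority over placebo, and the only between-arm comparison named for discrete harms is a chi-squared test in a trial not sized for harms, with no effect measure attached

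*SAP article*

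**What the plan says.** Four places in the SAP article bear on this.

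- **Framework** gives a single hypothesis type for everything: "The aim of the study is to assess the superiority of TUDCA over placebo in terms of efficacy and safety parameters".
- **Study objectives** words the safety objective differently: "to evaluate the long-term safety and tolerability of TUDCA". It contains no hypothesis of being better than placebo.
- **Statistical principles** sets one general rule, "Statistical significance will be determined by a two-sided *p*-value ≤ 0.05", with no separate rule for safety. It also promises intervals: "Confidence intervals at the 95% level (95% CI) will be reported for all outcomes and measures of association". The parenthesis that follows lists proportions, means, odds ratios and hazard ratios.
- **Safety/harms** plans listings by severity and by relationship to the drug, and summaries by arm: "The number and percentage of AEs will be reported, per treatment arm and overall, along with the number and percentage of participants" with at least one event. It then adds "Discrete safety endpoints will be compared using a chi-squared test", and "The denominator will be the safety population". Continuous safety endpoints go to a t-test or Mann–Whitney test.

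Under **Sample size**, power is given for the responder proportion and for survival. No safety endpoint is mentioned there.

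**The concern.** A superiority aim for harms asks whether TUDCA is safer than placebo. For an active drug added to riluzole, the useful question is how much extra harm the data can exclude, and the wording under Study objectives is closer to that question. The two statements should agree.

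The method follows the testing framework. A chi-squared test returns a p-value, but no size of excess and no upper limit. With the planned numbers, a non-significant result is the likely outcome for many harms even if TUDCA doubles them. Nothing in the text warns against taking such a result as reassurance. What is at stake is how the secondary objective on safety and tolerability will be read. The efficacy analyses are not affected.

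**Working it through.** **Inputs from the document.** Allocation is 1:1 (Randomization). On total size, "the enrolment was planned to be closed at 320 randomized patients" (Sample size), so there are about 320/2 = 160 per arm. The test is two-sided at 5%. The size of the safety population is not stated; 160 per arm is used as its planned size.

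**Assumed input.** The document gives no control-arm rates for any harm, so a range is shown.

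**1. The plan's own figure.** For 10% v 20% responders with 80% power, using the pooled-variance formula:

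n = [1.96·√(2·p̄·(1−p̄)) + 0.8416·√(p1(1−p1) + p2(1−p2))]² / (p2−p1)²

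With p̄ = 0.15: [1.96·√0.255 + 0.8416·√0.25]² / 0.01 = (0.990 + 0.421)² / 0.01 ≈ 199 per arm. This agrees with the stated 199, so the same method is applied to harms.

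**2. Power for a doubling from 5% to 10% at 160 per arm.** With p̄ = 0.075:

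[0.05·√160 − 1.96·√(2·0.075·0.925)] / √(0.05·0.95 + 0.10·0.90) = (0.632 − 0.730)/0.371 = −0.263

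Power = Φ(−0.263) = 39.6%. Exact enumeration of the Pearson chi-squared test over all binomial outcomes gives 39.4%. With a continuity correction the exact figure falls to 31.6%. With 144 per arm (10% lost) the approximation gives 36.3%. Reaching 80% would need 435 per arm.

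**3. Dependence on the assumed control rate** (160 per arm, exact, no continuity correction):

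| Control | TUDCA | Power | Doubling missed |
|---|---|---|---|
| 1% | 2% | 9.8% | 90% |
| 2% | 4% | 16.6% | 83% |
| 3% | 6% | 24.9% | 75% |
| 5% | 10% | 39.4% | 61% |
| 10% | 20% | 71.4% | 29% |
| 15% | 30% | 90.3% | 10% |

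**4. What the p-value hides.** Suppose 8/160 v 16/160 is observed, an exact doubling.

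- Chi-squared = 0.05² / (0.075·0.925·2/160) = 2.88, below the critical value of 3.84, so non-significant.
- Risk difference = 5.0 points. SE = √(0.05·0.95/160 + 0.10·0.90/160) = 0.0293. The 95% CI is 5.0 ± 1.96·2.93, or −0.7 to +10.7 points.
- If both arms showed 8/160, the interval would be ±1.96·√(2·0.05·0.95/160) = ±4.8 points.

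**5. Scope.** Continuous safety measures are much less affected. For a 0.5 SD shift, 0.5·√(160/2) − 1.96 = 2.51, which is about 99% power.

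**The case against.** The strongest reply is that this is ordinary descriptive safety reporting with one line of testing inside it. Much of that stands.

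- **No decision rule exists.** A reader might infer that the safety conclusion will rest on non-significance. The document does not say so. It sets no safety criterion or margin and nowhere treats p > 0.05 as showing safety. The tests are two-sided, so they can also flag harm.
- **The test is not all there is.** The plan includes listings by severity and relationship, counts and percentages by arm, concomitant medication, changes from baseline in vital signs and laboratory values, and a description by pandemic period. It would be wrong to say that nothing else informs the safety objective.
- **Intervals are promised.** Safety appears under Outcomes and as a row of the outcome assessment table, so the general promise of 95% CIs reasonably covers each arm's AE proportion. A reader might infer that no interval for harms will be produced; the text does not support that.
- **Low power for harms is usual.** It is not an error in itself, and no change of summary measure alters what 160 per arm can detect. The control rates above are assumptions.

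The reply leaves two things standing. The superiority wording for safety is an explicit statement, so it cannot be put down to condensing a longer plan. And although odds ratios appear in the general list of intervals, Safety/harms ties no between-arm measure to AEs. The comparison it does name is the one that says least about excess harm.

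**Conclusion.** The point holds as a defect of framing and of the named method. The superiority aim under Framework does not match the evaluative objective under Study objectives. For discrete harms, the only between-arm comparison specified is a chi-squared test at the general 5% level, with no effect measure.

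The size depends on the assumed control rate. At 160 per arm, a doubling is missed about 83% of the time at 2%, 61% at 5% and 29% at 10%. These figures assume the full 160 per arm and no continuity correction; fewer patients or a correction would raise them. Non-significance is therefore weak evidence on excess harm. The conclusion goes no further than that: the documents do not support a claim that the sponsor plans to declare TUDCA safe on a non-significant test.

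**What to change.** - **Framework:** limit superiority to efficacy and state the safety aim as estimation, in line with Study objectives.
- **Safety/harms:** for the AE summaries, report the between-arm risk difference (TUDCA minus placebo) with its 95% CI.
- **Safety/harms:** if p-values are kept, label them descriptive, and state that a non-significant result is not evidence of no harm.

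The cost is some rewording and one extra column in the AE tables. Data collection, sample size and efficacy analyses do not change. The safety statement will look less favourable, because the intervals will be wide.

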### Statistical interim analyses and stopping guidance

An interim analysis was originally scheduled only to verify the hypotheses specified in the study power calculation and to increase the sample size if needed. Nevertheless, due to the reassessment of the sample size resulting from the implementation of COVID-19 mitigation strategies, the interim analysis was consequently canceled.

### Timing of final analysis and outcome assessment

The final analysis will be conducted upon completion of the final visit of the last enrolled patient (Fig. 1). Blinding will be removed when all analyses have been performed, following a triple-blind scheme. The schedule for assessing outcomes is presented in Table 1.

**Fig. 1 Fig1:**
[figure not shown]
Timeline of the study and visit schedule

**Table 1 Tab1:** Outcome assessment

Visit	Lead-in			Double-blind trial					
Timescale	M-3	W-6	M0	M3	M6	M9	M12	M15	M18
ALSFRS-R	✓	✓	✓	✓	✓	✓	✓	✓	✓
ALSAQ-40 questionnaire	✓	✓	✓	✓	✓	✓	✓	✓	✓
FVC	✓	✓	✓	✓	✓	✓	✓	✓	✓
EQ-5D-5L questionnaire	✓	✓	✓	✓	✓	✓	✓	✓	✓
MRC sum-score	✓	✓	✓	✓	✓	✓	✓	✓	✓
Survival or respiratory insufficiency	✓	✓	✓	✓	✓	✓	✓	✓	✓
Blood biomarkers			✓		✓		✓		✓
CSF biomarkers			✓				✓		
Safety parameters	✓	✓	✓	✓	✓	✓	✓	✓	✓

*M* month, *W* week

## Statistical principles

Statistical significance will be determined by a two-sided *p*-value ≤ 0.05. Confidence intervals at the 95% level (95% CI) will be reported for all outcomes and measures of association (proportions, means, odds ratios and hazard ratios). Main analyses will be carried out on the intention-to-treat (ITT) population.

### Adherence and protocol deviations

The clinical sites will adopt all reasonable measures to ensure data collection in accordance with the protocol. However, practical circumstances may lead to some variations beyond the site’s control. Such deviations will be documented and summarized, along with the reason for their occurrence. Adherence to the study protocol is based on the proportion of completed visits to those scheduled and the proportion of scheduled doses that were consumed.

### Analysis population

ITT population is defined as all patients who were randomized into the study.

The per-protocol population includes those patients adherent to both visit and medication, respectively defined as patients who completed at least 80% of the expected routine study visits and consumed at least 80% of the prescribed assigned medication [10, 11].

Following the COVID-19 amendment (March 23, 2020), telemedicine visits were introduced as an alternative to in-person visits. For the per-protocol analysis purpose, these two modalities will be considered exchangeable.

The safety population (full analysis population) includes all subjects participating in the trial who received at least one dose of the trial medication. The safety population does not include subjects who dropped out before receiving any treatment.

## Trial population

### Eligibility

Eligible candidates are patients of any gender, aged 18 to 80 years, with probable or probable laboratory-supported, or definite ALS diagnosis according to the revised El Escorial ALS diagnostic criteria [12], having disease duration no longer than 18 months, vital capacity at least 70% of normal, stable on riluzole treatment for 3 months during the lead-in period, and have provided signed informed consent. The main exclusion criteria include cognitive impairment or psychiatric illness, active peptic ulcer, previous surgery, or infections of the small intestine. Detailed inclusion and exclusion criteria can be found in the study protocol [9]. All eligibility criteria must be met by the time of the randomization visit (month 0).

### Recruitment

The flow of study participants, including the number of subjects assessed for eligibility, excluded, randomized, allocated to treatment, withdrawn, or lost to follow-up, will be summarized in a Consolidated Standards of Reporting Trials (CONSORT) diagram (Fig. 2).

**Fig. 2 Fig2:**
[figure not shown]
TUDCA-ALS flow diagram (CONSORT 2010)

### Withdrawal/follow-up

Patients may withdraw from this study at any time. In case of withdrawal, research samples and data will continue to be stored and analyzed for future research, unless the patient specifically requests the withdrawal of samples. The timing and reasons of withdrawal and/or lost to follow-up (LTF) will be summarized, whenever possible, as time to event data and will be presented using Kaplan–Meier curves, both overall and by treatment group.

### Baseline patient characteristics

Patients will be described with respect to all variables collected at baseline (month 0, Fig. 1), separately for the two randomized groups. These variables include demographic information, medical and disease history, physical examination, vital signs, electrocardiogram results, FVC, ALSFRS-R, MRC sum-score, EQ-5D-5L, ALSAQ-40, hematological and biochemical parameters, and concomitant treatments. Categorical data will be summarized by numbers and percentages. Continuous data will be summarized by mean, standard deviation, range, median, and interquartile range. Tests for statistical significance will not be conducted for baseline characteristics; instead, any imbalances will be noted based on their clinical importance.

## Analysis

### Outcomes

The primary outcome is measured through the identification of the responder patients, defined as those showing an improvement of at least 20% in the ALSFRS-R slope during the 18-month randomization period compared to the 3-month lead-in period. Slope coefficients for ALSFRS-R decline will be calculated separately for the lead-in period and the treatment period using the linear regression model.

The secondary efficacy outcomes are presented in Table 2. The safety and tolerability of TUDCA will be evaluated through the assessment of adverse events, concomitant treatments, physical examinations, vital signs, and routine laboratory tests (hematology and biochemistry).

**Table 2 Tab2:** Secondary and exploratory outcomes

Variable	Description
**Clinical**	
ALSFRS-R score (*ALSFRS-R)*	ALS Functional Rating Scale Revised consists of 12 questions, each scored out of 4 points. A total score is calculated by summing the scores from each question with a maximum score of 48 (better performance, i.e., absence of the measured symptoms of ALS) and a minimum score of 0 (worst performance)
Survival time measured by death or respiratory insufficiency	Survival status is recorded at the end of study as well as respiratory insufficiency defined as tracheostomy or the use of non-invasive ventilation for ≥ 22 h per day for ≥ 10 consecutive days. Survival time is defined as the time elapsed between randomization and death from any cause and tracheostomy, whichever occurs first
Forced vital capacity score (FVC)	The index of respiratory function expressed as a percentage of the expected value is used to indicate potential respiratory compromise
Muscle force assessed by the Medical Research Council (MRC) scale	MRC score is a summation of the strength of 6 muscle groups tested on both sides ranging from 0 (paralysis) to 60 (normal strength)

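### Table 2 defines the survival event in two ways, with and without prolonged non-invasive ventilation, and the stated survival power belongs only to the version that includes it

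*SAP article*

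**What the plan says.** Four places in the SAP article bear on the survival event.

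- **Table 2, row label:** "Survival time measured by death or respiratory insufficiency".
- **Table 2, first sentence of the description:** "respiratory insufficiency defined as tracheostomy or the use of non-invasive ventilation", where the ventilation must be used for at least 22 hours a day over at least 10 days in a row.
- **Table 2, next sentence:** "Survival time is defined as the time elapsed between randomization and death from any cause and tracheostomy, whichever occurs first". NIV does not appear.
- **Sample size:** the planned 440 patients are said to give 83.3% power for a "13% absolute difference in survival (defined as death or respiratory insufficiency) between the two treatment groups", at a hazard ratio of 0.616. After the reduction to 320 patients, the text gives 80% power for a 14-point difference at a hazard ratio of 0.58.

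The visit schedule in Table 1 has a row called "Survival or respiratory insufficiency", ticked at every visit, without listing components. The section on analysis methods for primary and secondary outcomes speaks only of the survival outcome. It assigns Kaplan–Meier, the log-rank test and Cox models to it, and adds a joint test with ALSFRS-R. It does not say which events are counted.

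**The concern.** The label and the first sentence of the row make prolonged NIV an event. The sentence that sets the time origin and the end event does not. A statistician cannot program both. The definitions can differ in two ways:

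- A patient who reaches the NIV criterion and has neither died nor had a tracheostomy by month 18 is an event under one and censored under the other.
- A patient who reaches the NIV criterion and dies later is an event under both, but at different times.

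Every survival analysis in the plan inherits the ambiguity: Kaplan–Meier, log-rank, Cox and the joint test. So do the conditional analyses (restricted mean survival time if proportional hazards fails, censoring weights if COVID-19 censoring is not negligible) and the Cox models on slope and responder status. Survival is also the only secondary endpoint with its own power statement, and that statement is tied to the version with respiratory insufficiency. The article says that it exists to prevent selective reporting and data-driven analysis. An event definition that can be read two ways works against that aim.

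**Working it through.** **Inputs.** From Sample size: placebo survival of 60% at 18 months ("assuming an 18-month survival of 60% in the placebo group"), N = 440 with hazard ratio (HR) 0.616, and N = 320 with HR 0.58. From Randomization: 1:1 allocation. From Statistical principles: two-sided 5% significance. I apply this to survival, since the survival power sentence gives no alpha of its own.

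**Formulas.** With S0 and S1 the 18-month survival in the placebo and TUDCA arms:

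- S1 = S0^HR
- expected events d = (N/2) × [(1 − S0) + (1 − S1)]
- Schoenfeld power = Φ(√(d/4) × |ln HR| − 1.96)

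**Step 1: the plan's own figures, composite endpoint.**

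- N = 440, HR 0.616: S1 = 0.60^0.616 = 0.73. d = 220 × (0.40 + 0.27) = 147.4. Power = 83.7%, against 83.3% stated. Freedman's formula gives 82.2% and a comparison of two proportions 82.6%.
- N = 320, HR 0.58: S1 = 0.60^0.58 = 0.7436. d = 160 × (0.40 + 0.2564) = 105.0. Power = Φ(√(105/4) × 0.5447 − 1.96) = Φ(0.83) = 79.7%, against 80% stated.

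Both figures reproduce for an endpoint with 60% event-free survival on placebo, which the plan attaches to death or respiratory insufficiency. A difference of exactly 14 points would give HR = ln 0.74 / ln 0.60 = 0.589 and 77.5% power. HR 0.58 corresponds to 14.4 points, so this is a matter of rounding and nothing below depends on it.

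**Step 2: if death or tracheostomy is analysed instead.** The documents do not say how many composite events are NIV only. Two assumptions are needed: a share s of the placebo composite events is NIV with neither death nor tracheostomy by month 18, and the HR stays the same. Then S0 = 1 − 0.40 × (1 − s), and the formulas above apply. The s = 0 row is the composite itself.

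| s | S0 | Events, N = 320 | Power, N = 320, HR 0.58 | Power, N = 440, HR 0.616 |
|---|---|---|---|---|
| 0 | 0.60 | 105.0 | 79.7% | 83.7% |
| 5% | 0.62 | 99.5 | 77.6% | 81.7% |
| 10% | 0.64 | 94.1 | 75.2% | 79.5% |
| 20% | 0.68 | 83.3 | 70.0% | 74.5% |
| 30% | 0.72 | 72.6 | 64.1% | 68.6% |

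For example, at s = 10% and N = 320: S1 = 0.64^0.58 = 0.772, d = 160 × (0.36 + 0.228) = 94.1, and power = Φ(√(94.1/4) × 0.5447 − 1.96) = Φ(0.68) = 75.2%.

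**Step 3: which definition governs.** The row label and the power statement point to the composite, and the Table 1 label also names respiratory insufficiency. The only sentence that defines the time variable points to death or tracheostomy. The analysis section uses the word survival without a definition, so the text does not decide.

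**The case against.** The strongest reply is that the narrow sentence is the outlier and probably a drafting omission. The label and the power statement both use respiratory insufficiency, and the row sets exact NIV thresholds that would have no purpose if NIV were not an event. If the composite is analysed, the stated power applies as written. This stands, and it limits the point. It does not remove it, because the sentence left unaligned is the one a programmer would follow.

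Some stronger readings are tempting but go beyond the text:

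- A reader might infer that the stated power and event count are wrong for the analysed endpoint. The power mismatch arises only if the narrow sentence governs, which the article does not establish. It states no survival event count at all, so none can be wrong.
- A reader might take survival to be the main secondary endpoint. The plan gives no ranking: the objectives list survival first, and Table 2 lists ALSFRS-R first.
- A reader might fear that the definition will be chosen to favour one arm. Under the section on timing of the final analysis, blinding is lifted only after all analyses are done. That limits such a choice, although it does not fix the definition.

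The size of any power loss also rests on assumptions. A small NIV-only share costs about 2 points, and a different HR for the narrower endpoint could move power either way.

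**Conclusion.** The contradiction is real and lies within one table row: prolonged NIV is an event by the label and first sentence, and not by the survival-time sentence. No other section of the article resolves it. The 80% power at N = 320 and HR 0.58 is for death or respiratory insufficiency and reproduces for it (79.7%). It would not carry over to death or tracheostomy.

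How much would be lost cannot be known from the documents. With the HR held at 0.58, power would be about 78%, 75% or 70% for NIV-only shares of 5%, 10% or 20%. Both the shares and the constant HR are assumptions. The textual conflict is certain; the loss of power is conditional.

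This should be fixed. It concerns a secondary endpoint and leaves the primary responder analysis untouched.

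**What to change.** Before unblinding, reconcile the two sentences in Table 2. The choice that fits the rest of the plan is to amend the survival-time sentence to the composite already in the label and the power statement: time from randomization to the first of death from any cause, tracheostomy, or NIV meeting the criterion already in that row. State how the NIV event date is set from the data recorded. Death or tracheostomy can then be reported as a sensitivity analysis.

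If death or tracheostomy is what is intended, keep the sentence, correct the row label, and restate the survival power under Sample size for that endpoint, with its own assumed placebo survival.

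The text change is about one sentence plus the dating rule. Table 2 says that respiratory insufficiency is recorded, but the article does not say that the start date of a qualifying NIV period is captured. This should be checked against the case report form before the dating rule is written.
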